### Ethical Considerations

This study has been approved by the institutional review board (IRB) of Massachusetts General Brigham (2022P000580). Full informed consent will be obtained by the principal investigator (a licensed physician) prior to study activities. A data safety monitoring board is not needed for a minimal risk intervention (IRB determination). This study was registered on ClinicalTrials.gov (NCT06316804).

Protocol deviations are documented and reported to the IRB and sponsor based on Massachusetts General Brigham IRB policy. Minor deviations are reported at continuing review based on the designated timeline by the IRB. Any major deviations are reported at time of identifying the deviation based on the IRB policy. All participants will complete a virtual orientation visit (prior to baseline assessment). At this visit, waitlist participants and intervention participants are provided guidance on obtaining emergent or urgent referral services, including reaching out to the study team (which includes a social worker, resource specialist, and psychiatrist) at any time throughout the study period.

All participants complete full informed consent prior to study activities. The study is voluntary and participants may discontinue participation at any time. The study team will ensure participants are able to safely discontinue participation. Only deidentified information is used for analysis and publication purposes. To help with retention, starting at US $20 for the initial baseline assessment, we will offer a graded compensation schedule with US $5 to US $10 increments for subsequent assessments completed.

### Data Dissemination and Data Availability

The study results will be presented at conferences and in relevant journals. After data collection and initial analysis is completed and published, data will be managed based on sponsor (National Institutes of Health) data management and privacy policy. Deidentified data will be available in accordance with the National Institute of Mental Health Data Archive policy and timeline.

## Results

### Study Status

The study was funded on August 16, 2022. Initial activities involved app design. Following app design, clinical trial activities will be initiated. As of submission of the manuscript, 75 of 90 participants were successfully recruited. Study results will be published in March 2027.

### Study Outcomes

Our study will assess our ability to recruit and retain study participants and measure usability, satisfaction, and adherence. The primary outcome will be mental health service use, assessed 4 weeks after the intervention and at 3 months after the booster sessions and again at 6 and 12 months, following booster sessions. Secondary outcomes will include anticipated, enacted, and internalized stigma; medical mistrust; and help-seeking behavior. The primary outcome is defined as any engagement with mental health services: this includes intake appointments, follow-up appointments, or scheduled appointments for mental health with a psychiatrist, physician or clinician, clinical psychologist, therapist, or self-report mental health service use (verified by electronic health records). At baseline, participants sign a release of information (ROI) form to allow the study team to obtain their medical records from their designated health system. The ROI form expires at 6 months, and a new ROI will be obtained to ensure the study team is able to retrospectively review use of mental health services at study completion at 12 months.

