### Study Design and Setting

The study follows a single blind design among 2 experimental arms and 1 waitlist control arm. Participants are unaware of which intervention arm they are assigned among the two experimental arms. It was not feasible to fully blind the participants to the intervention versus waitlist arms, but we are able to blind participants to the specific content of the two intervention arms.

The intervention will involve short videos (6-12 minutes in length) of patients describing personal narratives of mental illness, treatment, and recovery and will be delivered over 4 weeks, with 2 booster sessions in weeks 6 and 12. Study participants (N=90) will be randomly assigned to 1 of 3 arms: a standard video-based app (n=30), a video-based app modified with a concordant patient video (n=30), and a waitlist control (n=30).

The study team used the SPIRIT (Standard Protocol Items: Recommendations for Interventional Trials) checklist in the development of the study protocol and conceptualization of the study and as study activities were initiated. We have included the page reference numbers for the SPIRIT checklist. The study team will follow the CONSORT (Consolidated Standards of Reporting Trails) checklist criteria throughout the study, including randomization scheme, study procedures, and planned analysis.

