#### Setting, Participants, and Eligibility Criteria

Recruitment will take place through the Massachusetts General Hospital patient registry, online social media advertising, and in partnership with community-based organizations. All participants will be prescreened via a phone call and/or an online form. All participants will complete an orientation call prior to randomization. To ensure representativeness of the sample, we will use a stratified random sampling of study participants to include equitable numbers of genders, migrant status, and ethnic origin (African Americans, African immigrants, Afro-Caribbean immigrants, and Afro-Latina). The participant eligibility criteria are shown in Textbox 1.

Participant eligibility criteria.

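### The 12-month record review of the primary outcome depends on each participant re-signing a release that lapses at 6 months, and self-reported care is tied to record verification, so ascertainment may be incomplete and possibly informative

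*Protocol article*

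**What the plan says.** All of this is in the protocol article. Study Outcomes defines the primary outcome as any engagement with mental health services. The definition covers several kinds of appointment and also "self-report mental health service use (verified by electronic health records". Table 1 (Assessments) names the electronic medical record as the only measure of this outcome.

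At baseline, participants sign a release that lets the team "to obtain their medical records from their designated health system". On its duration, Study Outcomes says: "The ROI form expires at 6 months, and a new ROI will be obtained". The stated purpose of renewal is to "retrospectively review use of mental health services at study completion at 12 months".

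The same section places the later assessments "again at 6 and 12 months, following booster sessions". Study Design and Setting describes delivery over 4 weeks "with 2 booster sessions in weeks 6 and 12".

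The Missing Data section plans to record reasons for dropout and to use multiple imputation for follow-up data missing at random.

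**The concern.** The main advantage of a record-based outcome is that it can be read for people who stop answering surveys. Here that advantage ends at month 6 unless the participant acts again. The people least likely to sign a second release are those who have disengaged from the study.

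The loss may also be related to the outcome. Willingness to release medical records plausibly depends on medical mistrust. The trial aims to lower mistrust, measures it as a secondary outcome and proposes it as a mediator. If mistrust affects both re-signing and use of services, missing at random is doubtful. This is an inference from the trial's own model, not something the article states.

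Verification raises a separate problem. Where a record is obtained but the participant was seen elsewhere, for example by an independent therapist, the record cannot confirm the self-report and true engagement may not be counted.

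The pilot's estimates are meant to inform a fully powered trial, so attenuated or biased estimates would carry forward.

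**Working it through.** **1. Which months the first release covers.** Inputs: release signed at baseline, expiry at 6 months, review at 12 months (Study Outcomes); boosters in weeks 6 and 12 (Study Design and Setting). Assume the intervention starts close to baseline.

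- If follow-up is counted from baseline, the 6-month assessment falls on the expiry date and the 12-month review falls 6 months after it.
- If follow-up is counted from the week-12 booster, 12 weeks is 12 × 12/52 = 2.8 months. The last two assessments then fall at 6 + 2.8 = 8.8 months and 12 + 2.8 = 14.8 months. Both come after the first release has lapsed, and the second comes after the stated 12-month completion.

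On either reading, the 12-month assessment needs the second signature. A review carried out only at the end also needs it to reach months 0-6, unless records were requested earlier.

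**2. The plan's power figure, as background.** Data Analysis and Power Calculation gives 72% power for d = 0.49 at α = .05 with 30 per arm. Sidedness is not stated. Take 60 pooled intervention participants against 30 controls:

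- SE = √(1/30 + 1/60) = 0.2236, and 0.49/0.2236 = 2.191.
- One-sided: Φ(2.191 − 1.645) = 70.8%, close to the stated 72%.
- Two-sided: Φ(2.191 − 1.960) = 59.1%.

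**3. Illustration: outcomes missing.** Assume 20% of each arm has no outcome at all, leaving 24 controls and 48 intervention participants:

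- SE = √(1/24 + 1/48) = 0.25, and 0.49/0.25 = 1.96.
- One-sided: Φ(1.96 − 1.645) = 62.4%. Two-sided: Φ(1.96 − 1.96) = 50.0%.

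The cost is 8 to 9 points. It would be smaller if months 0-6 were secured for these people.

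**4. Illustration: care not captured.** The article gives no engagement rates. Assume 20% in control; an arcsine effect of 0.49 then gives 42.35% in intervention. Assume also that uncaptured care is counted as no engagement, a rule the article does not state. If a share s is captured in both arms, the difference is s × (0.4235 − 0.20). Power is Φ{[Δ − z√(p̄(1−p̄)(1/30+1/60))] / √(p₁(1−p₁)/30 + p₂(1−p₂)/60)}, with 30 controls and 60 intervention participants.

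| Capture, both arms | Risk difference | Two-sided power | One-sided power |
|---|---|---|---|
| 100% | 0.224 | 56.0% | 69.1% |
| 90% | 0.201 | 49.1% | 62.7% |
| 80% | 0.179 | 42.2% | 56.1% |
| 60% | 0.134 | 29.4% | 42.5% |

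**5. Illustration: capture differing by arm.** The true risk ratio is 0.4235/0.20 = 2.12.

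- 90% capture in control and 70% in intervention: (0.4235 × 0.7)/(0.20 × 0.9) = 1.65.
- The reverse: (0.4235 × 0.9)/(0.20 × 0.7) = 2.72.

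The bias can go either way. Nothing in the documents says which way, or whether capture differs by arm at all.

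**The case against.** The strongest reply is that renewal is the investigators' own safeguard: they know the form expires and plan to obtain another. Months 0-6 are covered by the first release, and multiple imputation is planned. The article does not say who sets the 6-month limit, so lengthening it may not be in the team's hands. All of this stands. It narrows the point to people who do not re-sign and to the timing of the record request. No analysis rule can recover records the team has no permission to obtain.

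Four stronger readings are tempting, and the documents do not support them.

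- *Dropouts are scored as not engaged.* No section says so. A coding rule for unobtainable records may sit in the full protocol or analysis plan, which are not shown; its absence from an article is not a fault.
- *Recruits from outside the hospital are out of reach.* Recruitment does use "online social media advertising, and in partnership with community-based organizations", but the designated system is the participant's own, not the trial's network. Only care outside that system is affected.
- *Up to 18 of 90 lose half the outcome window.* That takes 20% × 90 from the dropout criterion in Planned and Interim Analysis. The criterion is a feasibility target for one or more conditions, not an upper limit, and it does not measure refusal to re-sign.
- *Weekly app prompts make loss differ by arm.* The weekly sessions run 4 weeks and the last booster is in week 12, well before renewal. The reminders for missed assessments (Recruitment) and the graded payments (Ethical Considerations) are not limited to one arm.

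The article also admits that the trial is underpowered, so lost power alone is not decisive.

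**Conclusion.** The point holds as a risk of incomplete, possibly informative, ascertainment of the primary outcome. Three parts rest directly on the text: the release lapses at 6 months, the 12-month review needs a second signature, and self-report is tied to record verification. That the loss is related to mistrust is an inference.

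The size cannot be derived from the documents. The 20% loss, the engagement rates and the capture shares above are all assumptions. The capture table further assumes that unconfirmed care counts as no engagement. The figures show the order of magnitude if such losses occurred; they are not predictions for this trial. The weakness is worth correcting because the change is cheap and a lapsed release may not be recoverable.

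**What to change.** 1. Where the institution's rules allow, use a baseline release valid to the final record review and covering each provider the participant names. For those already enrolled, offer the updated form at the next contact.
2. Otherwise, request months 0-6 records for all participants before the first release lapses. This is the step that protects data for people who later disengage, since they may not sign an updated form either.
3. Treat unobtainable records as missing under the planned multiple imputation. This does not remove bias if the loss is informative, which is why the first two steps matter more.
4. Add a sensitivity analysis that counts unverified self-reported use as engagement.

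The cost is an IRB form revision or an earlier round of record requests, plus one extra analysis. A few participants may decline a longer release. Unverified self-report is open to reporting bias, particularly as participants know whether they are on the waitlist, so it should remain a sensitivity analysis. With 75 of 90 participants recruited at submission, some first releases may already have lapsed, and delay reduces what can be recovered.

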### Data Collection and Outcomes

Data collection will be done through a secure Research Electronic Data Capture (REDCap; Vanderbilt University) database. Our app platform allows us to track and collect data on app engagement and usage metrics.

The secondary outcomes will be anticipated, enacted, and internalized stigma; medical mistrust; and self-reported help-seeking behavior. Feasibility outcomes will be assessed, including acceptability (USE and SUS), adherence (use metrics), and retention in the study (online assessments completed). We define a priori targets for the SUS and USE scales as usability scores >70, indicating good to excellent usability and mean scores on the USE scales (comparing the two experimental arms). We will measure study adherence based on the number of app logins and target at least one video session and assessment completed.

## Discussion

### Expected Findings

Black adults are known to have lower use of mental health services. In light of the increasing use of mobile devices, a self-administered antistigma mobile app has the potential to enhance accessibility and scalability of traditionally difficult to access stigma reduction tools. This manuscript describes the study protocol for an ongoing RCT to assess 2 intervention arms (a concordant and standard video-based stigma-reducing mobile app) compared with a waitlist control group. We hypothesize that individuals assigned to the intervention groups will be more likely to choose to engage in mental health services and report decreased stigma and decreased mistrust compared with the waitlist control group. Additional secondary outcomes will allow an estimate of the extent to which changes in anticipated or enacted or internalized stigma and medical mistrust mediate the intervention’s effect on the primary and secondary outcomes. Mediation analysis will be conducted to assess whether stigma (Reported and Intended Behavior Scale and Internalized Stigma of Mental Illness) and medical mistrust (Group-Based Medical Mistrust Scale) are potential mediators in the pathway between engagement in mental health care and the intervention [65,66,68,70,71]. Causal mediation analyses will be conducted to assess the relationships. The direct and indirect effects from the causal mediation analyses will be estimated. Percent of total mediation effect and 95% CI from each causal mediation analysis will be provided. We will use the SAS (SAS Institute) procedure CAUSALMED based on methods developed by Valeri and Vanderweele [72].

### Study Status

This is an ongoing randomized controlled clinical trial. Recruitment of participants started in July 2024 and is expected to be completed in July 2026 for the 1-year surveillance follow-up. The study is currently under protocol version 3 (approved in December 2024).

### Future Directions

Given the low uptake of mental health services for people experiencing early signs and emerging symptoms of mental illness, efforts to increase early access to mental health services will be met with ongoing significant barriers to mental health care use if stigma and medical mistrust are left unaddressed. Data from this pilot and feasibility randomized trial will provide critical information about the feasibility and acceptability of this intervention and preliminary efficacy estimates.

### Limitations

The sample size is insufficient to definitively test the effectiveness of the intervention for the primary outcomes. However, prior to making large investments in this line of study, delineating mechanistic targets and identifying key outcome assessments and measures will be critical to informing future investment in fully powered RCTs and implementation studies. The use of mobile technology varies across age groups. To address this limitation, we have chosen to include a narrow age group (aged 18-45 years) while we test the feasibility and acceptability of the mobile app.

### Conclusions

Despite the limitations, the next step is to further refine the intervention (based on this clinical trial) for testing in a fully powered randomized controlled effectiveness trial. Future studies will be adequately informed on the refined approach in testing the effectiveness and implementation of this mobile app and other similar mobile health apps across disease conditions and across populations at risk of worsening of disease due to treatment hesitancy and high stigma. While the study is underpowered to test effectiveness, this study will fill a critical public health gap created by the stigma that leads to delayed diagnosis, delayed entry into mental health treatment, and increased morbidity and mortality related to mental illness.

## Abbreviations

CONSORT: Consolidated Standards of Reporting Trails
HIPAA: Health Insurance Portability and Accountability Act
IRB: institutional review board
RCT: randomized controlled trial
ROI: release of information
SPIRIT: Standard Protocol Items: Recommendations for Interventional Trials
SUS: System Usability Scale
USE: usefulness, satisfaction, and ease of use
